**Methods/design:**

A target sample of 70 young people with physical disabilities (aged 8–17 years, ambulant with or without aid, residing in Adelaide) will be recruited. Participants will be randomly allocated to either intervention or control following completion of baseline assessments. Assessments are repeated at 8 weeks (immediately post intervention) and 20 weeks (12 weeks post intervention). The primary outcome is objective physical activity determined from 7 day accelerometry, and the secondary outcomes are exercise intention, physical self-worth, quality of life and fatigue. Analyses will be undertaken on an intention-to-treat basis using random effects mixed modelling.

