### Randomisation

Random allocation to the intervention or control condition will take place after participants have completed all aspects of their baseline assessment.

Since age is recognised to impact children’s activity levels [29], and impairment level is associated with activity level in children with physical disabilities [9], a stratified randomised allocation procedure is being used to ensure an even balance of age and impairment levels between groups. Given the recognised effect of season on physical activity [30], blocking is being employed to ensure a close balance of participants in the intervention and control conditions throughout the study period, as recommended by CONSORT [31].

Randomisation is being achieved using four sets of opaque envelopes (Set 1: ages 8–12 years, Gillette level 7 or 8; Set 2: ages 13–17 years, Gillette level 7 or 8; Set 3: ages 8–12 years, Gillette level 9 or 10; Set 4: ages 13–17 years, Gillette level 9 or 10). Each set includes six envelopes, with three containing control allocation, and three containing intervention allocation. Randomisation is being undertaken by CM, who is provided with the participants’ ID number, age, and Gillette level, and who has no direct contact with participants.

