### Control condition

Participants randomised to the control condition are being told that their health will be monitored for 20 weeks, and are placed on a waiting list and provided with the full StepUp program at completion of the study.

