### Program evaluation

Participants’ experiences and views regarding the StepUp program are being evaluated using a purpose-designed feedback survey (Additional file 1). At the end of the intervention, participants in the intervention group are invited to complete a 13-item feedback form, containing a combination of Likert-scale and open-ended items regarding what they thought of the various elements of the program, and what they liked, disliked and ideas for improvement. Participants’ daily step counts throughout the 6-week program are collected by the physiotherapist during the phone call and face-to-face appointments, and will be used to determine engagement and adherence with the program.

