### Analysis

A priori power analyses indicate that a sample of 42 will be required to detect a medium size within-between group interaction (f = 0.20), while a sample of 74 will be required to detect a small-medium size within-between group interaction (f = 0.15), assuming three repeated measures, two groups, an alpha-level of 0.05 and power of 80%. The change in outcomes from baseline to 8 weeks and 20 weeks, within and between groups, will be analysed using random-effects mixed-modelling, on an intention-to-treat basis. The relationship between primary and secondary outcomes and demographic variables will be assessed and where relationships exist the demographic variables will be used as covariates.

Data from the feedback survey and engagement data will be analysed descriptively. In addition, sub-group analysis will be undertaken to determine whether the intervention effectiveness is related to engagement/adherence.

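### The sub-group analysis by adherence rests on a post-randomisation, intervention-arm-only variable and is liable to show an apparent benefit in adherers even if the programme has no effect

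*Protocol article*

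**What the plan says.** All references are to the protocol article.

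- **Analysis.** Changes in outcomes to 8 and 20 weeks "will be analysed using random-effects mixed-modelling, on an intention-to-treat basis". Feedback and engagement data are to be described. Beyond that, "sub-group analysis will be undertaken to determine whether the intervention effectiveness is related to engagement/adherence".
- **Program evaluation.** "Participants’ daily step counts throughout the 6-week program are collected by the physiotherapist during the phone call and face-to-face appointments", and these counts "will be used to determine engagement and adherence with the program". No metric, cut-off or comparison group is given.
- **Randomisation.** "Random allocation to the intervention or control condition will take place after participants have completed all aspects of their baseline assessment".
- **Control condition.** Controls "are placed on a waiting list and provided with the full StepUp program at completion of the study".
- **Abstract, Methods/design.** "The primary outcome is objective physical activity determined from 7 day accelerometry".
- **Description of the intervention, Table 1.** Step goals are set as a 5% or 10% rise on the child's own previous week, and a wall chart records the days on which the goal was met.

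**The concern.** The stated aim is inferential: to establish whether the programme's effectiveness depends on adherence. A valid answer needs like compared with like. Adherence is observed only in children already allocated to StepUp, and a control child has no corresponding value. Comparing adherers with controls sets a self-selected part of one arm against the whole of the other. Comparing adherers with non-adherers drops the control arm altogether. In both cases motivation, health and each child's own activity trajectory can produce the difference.

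Step counts add to the problem. A child whose activity is rising for any reason will log more steps, meet more goals, and tend to show a larger accelerometer change at week 8.

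At stake is a secondary claim that the programme works in those who engage. The Discussion expects 40–70 participants, while the Analysis section requires 74 for f = 0.15. An inconclusive main result is therefore plausible, and such a claim would then attract attention.

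**Working it through.** **1. The plan's own figures.** The only numbers in the Analysis section are N = 42 (f = 0.20) and N = 74 (f = 0.15), for three measures, two groups, alpha 0.05 and 80% power. For the within-between interaction, λ = f²·N·m/(1−ρ), df1 = (k−1)(m−1) and df2 = (N−k)(m−1), with m = 3 and k = 2. The article gives no ρ; 0.5 is assumed.

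- N = 42: λ = 0.04 × 42 × 3/0.5 = 10.08, df 2 and 80, power 80.3%.
- N = 74: λ = 0.0225 × 74 × 3/0.5 = 9.99, df 2 and 144, power 80.6%.

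Both figures reproduce. They concern the randomised comparison; the sub-group analysis has no figure to reproduce.

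**2. Status of the adherence variable.** Allocation follows baseline, and step counts are logged during the programme, so adherence is post-randomisation. Controls wait until the study ends, so no matching control subgroup can be formed.

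**3. Size of the bias when the programme does nothing.** Let B be baseline activity, Y week-8 activity and A adherence, each with variance 1. Let corr(B,Y) = ρ = 0.5, corr(A,Y) = r and corr(A,B) = b. All of these correlations are assumptions. Take a median split on A and call the upper half the adherers.

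- Mean of A in the upper half: √(2/π) = 0.798.
- SD of change Y − B: √(2 − 2ρ) = 1.
- Expected false difference in change, adherers minus controls: 0.798(r − b).
- Adherers minus non-adherers: 2 × 0.798(r − b) = 1.596(r − b).
- Adherers minus controls, adjusted for baseline: 0.798(r − ρb).

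*Adherence as goals met* (taken as unrelated to baseline, b = 0). For r = 0.3, 0.5 and 0.7 the false difference is 0.24, 0.40 and 0.56 SD against controls, and 0.48, 0.80 and 1.12 SD between adherers and non-adherers.

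*Adherence as absolute step level* (b = r). The false difference in change is 0 at every r. Adjusted for baseline, it is 0.798 × 0.5r = 0.12, 0.20 and 0.28.

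**4. Chance of a nominally significant false benefit.** Simulation with 35 per arm (target 70, equal allocation) and t-tests; 2.5% is the unbiased value, and simulation error is about one percentage point.

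| Adherence metric and comparison | r = 0.3 | r = 0.5 | r = 0.7 |
|---|---|---|---|
| Goals met, high v low, change | 28% | 69% | 97% |
| Goals met, high v controls, change | 12% | 27% | 50% |
| Step level, either comparison, change | 2.5% | 2.5% | 2.5% |
| Step level, high v controls, baseline-adjusted | 7% | 12% | 19% |

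Hand check at r = 0.5, goals met, high (17 children) against controls (35): SE = √(1/17 + 1/35) = 0.296 and 0.40/0.296 = 1.35. The chance of exceeding 1.96 is then 1 − Φ(0.61) = 0.27, as simulated.

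With r = 0.1 and goals met, the chances are 6% (high v low) and 5% (high v controls). With 21 per arm (42/2), high v low gives 17%, 44% and 82%.

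An intermediate case links adherence to baseline only through week-8 activity (b = ρr). Counting both directions (nominal 5%), change scores then give about 7%, 10% and 15% against controls, and 11%, 21% and 37% for high v low.

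**The case against.** The strongest reply is that the article fixes neither the adherence metric nor the comparison, and that a condensed article may leave both to a fuller document. Step records could be used simply to count weeks logged, which ties adherence much less closely to activity. The median split and the contrast with all controls are illustrative choices, not the plan's. The Analysis section also works with change from baseline. If adherence meant absolute step level, equally related to baseline and week 8, change scores would show no bias at all.

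Much of this stands, and it rules out three stronger readings.

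- *A reader might infer that the analysis is bound to show a benefit.* It is not. The bias needs adherence to relate to week-8 activity beyond what the outcome scale removes, and the calculated chance runs from 2.5% to 97%.
- *A reader might call the analysis circular.* Steps come from a pedometer during the six programme weeks; the outcome comes from an accelerometer at weeks 8 and 20. The two are closely related but are not the same measurement.
- *A reader might blame pre-existing activity level alone.* On change scores, that mechanism gives no inflation in the step-level case above.

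The reply does not dispose of the point. The article itself states the source of the adherence variable and the inferential purpose, and carries no caution that the comparison is non-randomised. Because Table 1 sets goals relative to the child's previous week, meeting a rising personal target is a natural adherence metric, and that is the case with the largest bias. Adjusting for baseline is no cure: it leaves a bias in the step-level case that change scores would have removed.

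**Conclusion.** The concern holds as a liability to bias. As worded, the sub-group analysis cannot establish whether effectiveness depends on adherence, because its grouping variable is post-randomisation, confined to one arm and close in construct to the primary outcome.

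The size rests on assumed correlations (baseline to week 8 of 0.5; adherence to week 8 of 0.3 to 0.7), a median split and 35 per arm. Under these assumptions the range is from no inflation to a false benefit in almost every trial, so the unspecified metric and comparison largely decide the outcome.

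A reader might also infer that the trial's main conclusion is at risk. The documents do not support that: the primary analysis is separate and by intention to treat, and no primary conclusion is tied to the sub-group result. The point is a moderate, inexpensive improvement and not a condition for the trial to proceed.

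**What to change.** 1. Define adherence before outcome data are examined, by exposure to the programme (visits and calls completed, weeks logged), and not by step level or goals met. This loosens the tie to the outcome but does not restore randomisation.
2. Report the association of adherence with outcome within the intervention arm, adjusted for baseline activity, as exploratory and non-causal. Do not present it as effectiveness in adherers; change the stated aim from determining to exploring.
3. If a causal answer is wanted, add a complier-average or principal-stratum estimate based on randomisation as a sensitivity analysis. State its exclusion assumption, which is doubtful here because partial adherers still have the pedometer and handbook. Note too that it estimates an effect in compliers, not how the effect varies with engagement.

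Cost: revised wording, a short adherence definition and, if step 3 is taken, one further model. No new outcome data are needed. The secondary claim becomes weaker, and a complier-average interval will be wide at this sample size.

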## Discussion

Physical activity is important for physical and psychological health, as well as for maintenance of physical function and independence in young people with physical disabilities. Despite this, there have been few rigorous studies aimed at intervening on physical activity in this population.

This project will evaluate the effectiveness of a novel pedometer-based physical activity self-management program for young people with physical disability.

Strengths and weaknesses of the StepUp study warrant discussion. The StepUp intervention has been carefully designed by a team of researchers and clinicians, which includes researchers with expertise in physical activity measurement, physical activity intervention, childhood physical disability, the development of written materials for children with learning difficulties, as well as highly experienced clinicians (physiotherapists and a psychologist). The program has been specifically designed to be low-cost and low-touch in nature, so that if it is found to be effective, it can be readily incorporated into ongoing clinical services. A strength of the study is that it involves a rigorous randomised controlled trial design, incorporating high quality outcome measures, including objective measurement of physical activity. The StepUp study is a single-site study. For budgetary and feasibility reasons, the study can only sample from a finite population (young people with physical disabilities meeting the eligibility criteria, including residing in Adelaide). We intend to invite the entire eligible population, and anticipate 40–70 participants will join the study, with a priori power analyses suggesting a sample of this magnitude should be sufficient to detect small to moderate effects, should they be present. For budgetary reasons, the follow up is only 20 weeks from baseline (12 weeks post end of intervention). Should the results of this study be affirmative, in the future it would be beneficial if the intervention could be evaluated in a larger sample, and over a longer-term period, in a multi-centre trial.

This study forms an early attempt at developing and evaluating a feasible physical activity intervention for children with physical disabilities, and findings will inform future efforts in this field, to assist young people with disabilities to achieve the benefits of physical activity.

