### Study sample

The study will aim to enrol 50–70 participants. Participants are being recruited through Novita Children’s Services, the major provider of community-based therapy, equipment and family support services to young people with disabilities and special needs aged 0–18 years in the state of South Australia. Novita clients are eligible to participate if they (1) have a physical disability, (2) are aged 8–17 years, (3) have mild-to-moderate levels of physical disability (able to ambulate in the community with or without assistance; Gillette Functional Assessment Questionnaire levels 7, 8, 9 or 10 [18]), (4) live in or near Adelaide, Australia, and (5) are considered by their parent to have cognitive ability to understand the program. Exclusion criteria are (1) recent or planned medical and/or orthopaedic intervention (e.g. surgery or botulinim toxin injections) impacting ability to be physically active, and (2) injury impacting on ability to partake in physical activity. Recruitment is taking place on a rolling basis from June to December 2013.

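### The Discussion says 40–70 participants suffice for small to moderate effects, but the Analysis section's own power calculation supports this only for the medium effect, from 42 upward

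*Protocol article*

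**What the plan says.** The Analysis section gives two requirements: "a sample of 42 will be required to detect a medium size within-between group interaction (f = 0.20") and "a sample of 74 will be required to detect a small-medium size within-between group interaction (f = 0.15"). The conditions are "assuming three repeated measures, two groups, an alpha-level of 0.05 and power of 80" per cent.

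The sample size appears in three places:

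- Abstract, Methods/design: "A target sample of 70 young people with physical disabilities".
- Study sample: "The study will aim to enrol 50–70 participants".
- Discussion: the authors "anticipate 40–70 participants will join the study". The same sentence goes on to claim that this number is enough, citing "a priori power analyses suggesting a sample of this magnitude should be sufficient to detect small to moderate effects".

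The Discussion presents this last statement as support for a sample drawn from a finite population and limited by budget and feasibility.

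**The concern.** The Discussion cites the power analyses for a conclusion that they do not give across the range it names. The smaller of the two effects needs 74 participants, and no number from 40 to 70 reaches that. The larger effect needs 42, so 40 falls just short. The Analysis section has no calculation for any effect below f = 0.15, so the word small, used without qualification, has nothing behind it.

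What is at stake is a stated property of the design. The sentence tells readers what the trial can detect with the numbers it expects. If recruitment ends near 40 or 50, a reader who relies on it would think the trial adequately powered for the small-medium effect when power is between one half and two thirds.

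**Working it through.** **Inputs from the article.** Three repeated measures (m = 3), two groups (k = 2), alpha 0.05 and power 80% (Analysis). Allocation is 1:1: "Each set includes six envelopes, with three containing control allocation, and three containing intervention allocation" (Randomisation).

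**Inputs not in the article.** The correlation between repeated measures (ρ) and the sphericity correction (ε) are not given. I took ρ = 0.5 and ε = 1 because they reproduce both stated sample sizes.

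**Formula.** For the group-by-time interaction in a repeated-measures analysis of variance, the F test has

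- df1 = (k − 1)(m − 1) = 2,
- df2 = (N − k)(m − 1) = 2(N − 2),
- noncentrality λ = f² × N × m × ε / (1 − ρ) = 6 f² N at ρ = 0.5.

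Power is the probability that a noncentral F with these parameters exceeds the 5% critical value.

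**Step 1: reproduce the plan's figures.**

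- f = 0.20, N = 42: λ = 6 × 0.04 × 42 = 10.08, df2 = 80, power 80.3%.
- f = 0.15, N = 74: λ = 6 × 0.0225 × 74 = 9.99, df2 = 144, power 80.6%.

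These are the smallest totals with equal arms that reach 80%, so 42 and 74 are confirmed. Other correlations do not return the pair: ρ = 0.4 gives 50 and 88, and ρ = 0.6 gives 34 and 60.

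**Step 2: power at the sample sizes the article names.**

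| N | f = 0.10 | f = 0.15 | f = 0.20 |
|---|---|---|---|
| 40 | 26% | 52% | 78% |
| 50 | 31% | 62% | 87% |
| 70 | 43% | 78% | 96% |

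For example, at N = 40 and f = 0.15, λ = 6 × 0.0225 × 40 = 5.40 with df2 = 76, and power is 52.0%. Reaching 80% for f = 0.10 needs about 164 participants.

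**Step 3: smallest f with 80% power.** About 0.204 at N = 40, 0.182 at 50 and 0.153 at 70.

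**Step 4: conversion to SD units, under stated conditions.** Suppose the arms do not differ at baseline and differ by d SD at both follow-ups, where SD is the between-child SD at one visit. The differences (0, d, d) have mean 2d/3. The centred values are −2d/3, d/3 and d/3, and half of each falls to each arm. Then f² = (1/3)(1/4)(4/9 + 1/9 + 1/9)d² = d²/18. A difference at one follow-up only, (0, d, 0), gives the same result. Hence d = f × √18:

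- N = 70: 0.153 × 4.243 = 0.65 SD.
- N = 40: 0.204 × 4.243 = 0.87 SD.
- The plan's f = 0.15 and f = 0.20: 0.64 and 0.85 SD.

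For a linear (0, d/2, d) or half-fading (0, d, d/2) pattern, f = d/√24, and the plan's two values correspond to 0.73 and 0.98 SD at the largest follow-up difference.

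**Step 5: loss to follow-up, illustration only.** The article gives no rate. If 15% were lost, 70 enrolled would leave about 60 (70 × 0.85 = 59.5), and power for f = 0.15 would be about 71%.

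**The case against.** The best defence is that the headline gap is small. Pairing the ends of the range with the two requirements, 40 against 42 and 70 against 74 each give 78% instead of 80%. The Discussion's language is approximate, and at 70 the detectable f is 0.153 against the planned 0.15. This stands: at the Abstract's target there is no practical shortfall. It does not rescue the sentence, which applies to the whole range and covers the smaller effect too.

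The three sample sizes can also be read together: a target, an enrolment aim and a forecast, all topping out at 70. That is fair. They are untidy rather than in flat conflict, but they leave unclear which number the power claim belongs to.

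Three stronger readings are tempting, and the article does not support them.

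- *That f = 0.15 and 0.20 are really moderate-to-large differences of 0.64 to 0.85 SD, so the labels are wrong.* The conversion is correct only for particular effect patterns, the 2-df interaction test and ρ = 0.5. The article states no pattern and sets no SD benchmarks, and the Discussion's wording broadly follows the Analysis section's labels.
- *That the design cannot detect smaller differences.* The figures describe the interaction test used for planning. The analysis planned is a mixed model with covariates, and the article does not say whether the test is the omnibus interaction or a single contrast. As an illustration with ρ = 0.5 and a sustained effect, 80% power at N = 70 is reached at 0.59 SD for a 1-df averaged-change contrast and at 0.48 SD if that contrast is also baseline-adjusted. The article does not base its power statement on such an analysis.
- *That omitting an attrition allowance is an error, or that a null result will be misreported.* A condensed article may leave the allowance to the full protocol, and nothing in the text says how a null result would be read.

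**Conclusion.** The Discussion sentence is wrong as written. The plan's own calculation supports adequacy for the medium effect from 42 participants upward. It does not support 80% power for the small-medium effect at any number in the three stated ranges, and it says nothing about smaller effects. The deficit for f = 0.15 is about 2 points at 70, 18 points at 50 and 28 points at 40; for f = 0.20 it is about 2 points at 40 and none at 50 or above.

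These figures rest on ρ = 0.5 and sphericity, which are inferred. A different correlation would change them, but the stated 42 and 74 would then no longer hold. They assume complete data. This is a correction to a stated property and leaves the design, allocation and analysis untouched.

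**What to change.** Use one target, 70, in the Abstract, Study sample and Discussion. If a lower recruitment forecast is kept, label it as a forecast.

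Replace the Discussion's sufficiency claim with the delivered figures. Suggested wording: *Before any loss to follow-up, and assuming a correlation of 0.5 between repeated measures, the interaction test has 80% power for f of about 0.153 with 70 participants, 0.182 with 50 and 0.204 with 40. The sample is adequate for the medium effect (f = 0.20) from 42 participants upward; the trial is not powered for small effects.*

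If an SD equivalent is added, give its conditions: about 0.65 SD at 70 and 0.87 SD at 40, for a between-arm difference sustained at both follow-ups or present at only one, with the 2-df interaction test and correlation 0.5. Label any attrition-adjusted figure as an assumption.

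The change is wording only. The stated power becomes less favourable, and no extra participants are needed.
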